26 Description in protocol V1.3, dated 10.08.2022:

27 *For the monogenic positive FH group, we calculated that it will be necessary to include 41*  
28 *families per group to show a statistically significant difference between the two groups with a*  
29 *significance level of 5% and a power of 90%, assuming that the consent rates for the control and*  
30 *interventional groups will be in mean equal to 0.15 respectively 0.3 and will be at 95% in the*  
31 *intervals [0.1,0.2] (range 0.05) respectively [0.1,0.5] (range 0.2) and that the number of*  
32 *contactable relatives will be in mean equal to 4.*

33

34 All other changes were minor, unrelated to the scientific outcomes, and aimed at strengthening  
35 participant data protection in accordance with ethical requirements.

36

37 The trial protocol originally included a second randomized controlled trial to be conducted  
38 among index cases with negative genetic test results, namely those with probable polygenic  
39 familial hypercholesterolemia, using cascade lipid profile testing. However, this additional RCT  
40 was not carried out due to insufficient family participation in the pilot study.

41

42

### 43 **Final statistical analysis plan**

#### 44 **1. Introduction and purpose**

45 The CATCH study is a prospective randomized open-label multicenter implementation trial that  
46 promotes family genetic cascade screening in Switzerland. Each family from an adult older than  
47 16 years with a newly diagnosed pathogenic variant for familial hypercholesterolemia (FH) is  
48 randomly assigned to a multigenerational patient-mediated genetic cascade screening (1:1) either  
49 via the possibility to use of a web-based platform designed to send pre-prepared text messages or  
50 emails, and allowing to connect to a specialized clinical center, or a genetic cascade screening  
51 via the local procedure. The aim of the study is to show that the proportion of family members

52 who participate to the screening among those eligible is higher in the experimental group than in  
53 the control group.

54

55 *2. Objectives and endpoints*

56 The primary outcome is the uptake of cascade screening, defined as the number of genetic tests  
57 performed by family members within 6 months after referral, over the number of eligible first-  
58 degree relatives.

59

60 The secondary outcome is the proportion of new cases identified, defined as the number of  
61 positive tests detected within 6-months of referral among family members over the number of  
62 eligible relatives.

63

64 The primary and secondary outcomes must be assessed after accounting for family clusters.

65

66 *3. Analysis populations*

67 The population of interest consists in relatives of positive index cases who live in Switzerland  
68 (or are able to visit one of the study centre) and are aged 5 years or older. They must be a first-  
69 degree relative of a positive subject in their family, either the index case (cycle 1) or another  
70 positive relative (cycle > 1).

71

72 The primary and secondary outcomes will be primarily assessed using the Intention-to-treat  
73 (ITT) principle. However a per-protocol (PP) analysis will also be carried out for information.

74

75 *Intention-to-treat (ITT):*

All relatives will be assigned to the same group as their index case, irrespective of actual use of the web-based screening platform. In the ITT analysis, all family members thus belong to the same group.

#### *Per-protocol (PP):*

Relatives in the control group will remain in the control group as they have no access to the web-based communication platform. However, those relatives initially assigned to the intervention group but who will be contacted outside of the web-based platform by their referent will also be considered as part of the control group. In the PP analysis, relatives of index cases originally assigned to the intervention group may thus be part of the control or the intervention group, depending on how they were contacted by their referent.

#### *4. Primary analysis*

Baseline characteristics of index cases and participating relatives will be summarized using the median and interquartile range for continuous variables, and with counts and percentages for categorical variables. Differences between the intervention and control groups will be assessed using the Kruskal-Wallis test statistic for continuous variables, and the  $\chi^2$  test statistic for categorical variables. Characteristics of index cases in the two groups will be compared using standard asymptotic versions of these tests (i.e. for independent data). On the other hand, characteristics of the relatives will be compared after reconstructing the distribution of the test statistics under the null hypothesis using 1000 approximate permutation tests with group allocation permuted at the family level (between-family permutations). When comparing characteristics of relatives depending on the result of the genetic test, permutations of test result will be carried out between relatives from the same family (within-family permutations).

The probabilities of participation and detection as well as their 95% confidence intervals (CI) will be estimated using generalized estimating equations (GEE), using an exchangeable correlation structure to account for the data dependence induced by the family clusters. The model allows estimation of marginal probabilities of participation/detection in each arm (i.e. average probability at the population level), as well as the marginal odds ratio comparing the two arms.

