#### Modelling:

In the protocol V1.3, dated 10.08.2022, participation to screening (i.e. primary outcome) was modelled using a logistic mixed effect regression model, using the group as fixed effect and the family as random effect. In the final statistical analysis plan, we proposed to rather use generalized estimating equations (GEE) in order to estimate the marginal probability of participation/detection. This change has been motivated for two reasons. First, interest lies primarily in marginal probabilities (i.e. estimated at the population level) rather than conditional probabilities (i.e. within families) as estimated from mixed effect models. Secondly, unlike mixed effects models, GEE are robust to misspecification of the covariance structure in the data, which makes this approach appealing when the covariance structure is not of particular interest.

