## 2 BACKGROUND AND RATIONALE

Familial hypercholesterolemia (FH) is a genetic disorder associated with an increased risk of early-onset myocardial infarctions. In Switzerland there are about 40,000 subjects with FH, but only a minority of them are known. Unfortunately, many patients with FH are only diagnosed at the time of hospitalization for acute coronary syndrome. Because effective lipid-lowering drug can reduce the cardiovascular risk, this underdiagnosis is a major missed opportunity for prevention.

FH is transmitted to family members with a autosomal dominant mode. Therefore, each first degree relative of an index case has a 50% chance of having the disorder. To improve detection of patient with FH, the use of genetic test and cascade screening programs among relatives has been recommended by recent European and US guidelines for dyslipidemia and FH. The Centers for Disease Control also classified FH as a Tier 1 condition, and recommend the implementation of cascade screening as outlined in the National Institute for Health and Clinical Excellence (NICE) guidelines for identification and management of FH.

However, little is known about effectiveness of a FH screening programme in Switzerland. The implementation of a multicenter cascade screening program for FH has never been tested. First, it is unknown what would be the best method to contact at-risk relatives to improve the yield of FH detection. Because FH increase the life-long cardiovascular risk and can be effectively treated with lipid-lowering drugs and appropriate diet, physicians should ideally inform relatives of an index case of their potential cardiovascular risk and their options to reduce it. However, legal protection to guarantee privacy of data do not authorize physicians to directly contact at-risk relatives of an index case. Alternatively, the index case can be counselled to inform his relatives about the risk of FH. However this process can be hampered by inefficient family communication. Therefore, ethical tension exists between motivation to promote health care and interest in maintaining privacy of health information. This study is designed to test a contact program of relatives initiated by the index case, but actively supported by the healthcare team.

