#### *Differences between the monogenic positive and negative groups*

The test used for cascade screening will be different for relatives of index cases with monogenic *positive* FH and for relatives of monogenic *negative* FH index case.

a) *Relatives of a monogenic positive FH index case*

We will use a genetic and a lipid test to diagnose FH according to guidelines. If the patient refuse to perform a genetic test, a lipid test only will be used. If the genetic test is positive, the family tree will be completed with the patient and a second cycle of cascade screening will be performed (see **Figure 2**). If the genetic test is negative, the cascade screening will stop. There will be a maximum of three cycle of identification. For each genetic test done, study center will organize a pre and post-test counselling visit.

b) *Relatives of monogenic negative FH index case*

We will use a lipid test only to diagnose FH according to guidelines. For adults, the diagnosis of FH will be based on established LDL-c criteria available online <https://www.nice.org.uk/guidance/cg71/evidence/full-guideline-appendix-f-pdf-241917811>.

- For children from 5 years to 15 years old, diagnosis of FH will be based on a documented untreated/treated LDL-cholesterol of 4.0/3.0 mmol/l or above, or 3.5/3.0 mmol/l or above in case of a family history (see paragraph above for details).

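### The exchangeable GEE does not estimate the per-arm uptake defined as the primary outcome, because a family's eligible count grows with its own uptake

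*Combined protocol and SAP*

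**What the plan says.** SAP section 2 (Objectives and endpoints) defines uptake as the genetic tests "performed by family members within 6 months after referral, over the number of eligible first"-degree relatives. SAP section 3 (Analysis populations) lets a person into the denominator as a first-"degree relative of a positive subject in their family, either the index case (cycle 1) or another" positive relative in a later cycle. Protocol section 4.3 (Differences between the monogenic positive and negative groups) gives the rule that adds them. After a positive genetic test, "the family tree will be completed with the patient and a second cycle of cascade screening will be performed"; after a negative test the cascade stops. The limit is stated as "There will be a maximum of three cycle of identification".

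SAP section 4 (Primary analysis) estimates the participation and detection probabilities with 95% confidence intervals by GEE, "using an exchangeable correlation structure to account for the data dependence induced by the family clusters". It describes the results as marginal, population-level probabilities per arm plus a marginal odds ratio. The Modelling entry in the summary of changes defends GEE partly because "GEE are robust to misspecification of the covariance structure in the data". Protocol section 3.2 frames the primary outcome as a between-arm difference in this yield.

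Neither document discusses cluster size that depends on the outcome, or whether relatives or families should carry equal weight. Cycle appears only as a subgroup factor (SAP section 5).

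**The concern.** The endpoint is a ratio of totals in which every eligible relative counts once. The planned estimator does not count them equally, and the relatives it discounts are concentrated in families that grew because their members came forward and tested positive. Cluster size is therefore informative about the outcome.

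The robustness cited for GEE concerns the covariance model. It protects the estimate when the mean does not depend on cluster size. When it does depend on it, the choice of working correlation changes which average is estimated, and a robust variance then gives an interval around that other average.

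At stake are the absolute uptake figures, which are what users of an implementation trial will read first. The shortfall is also larger in the arm with more uptake, so the risk difference shrinks.

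**Working it through.** **1. Inputs.** From the documents: mean uptake 0.15 v 0.30 and a mean of 4 contactable relatives per family (protocol 5.1); ICC 0.2, family-level prediction intervals of 9–22% and 20–41%, and 44 families per arm (summary of changes, Sample size); at most three cycles (protocol 4.3). For the chance that a tested relative is positive, protocol section 2 says "each first degree relative of an index case has a 50% chance of having the disorder". Assumed, because the documents do not give them: 1 to 3 new eligible relatives per positive, beta-distributed family uptake that is constant over cycles, and full follow-up of every cycle.

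**2. The plan's own figure, and which ICC it reflects.** The standard two-proportion formula (two-sided 5%, 90% power) gives 161 relatives per arm. With design effect 1 + (4 − 1) × ICC and 4 relatives per family:

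- ICC 0.2: 161 × 1.6 / 4 = 64.4, so 65 families. With 44 families power is about 76%.
- ICC 0.02: 161 × 1.06 / 4 = 42.7, so 43 families, close to the stated 44.

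The prediction intervals also point to the smaller value. Control: (logit 0.22 − logit 0.09) / 3.92 = 0.267, and 0.267² / (0.267² + π²/3) = 0.021. Intervention: 0.261, giving 0.020. On the observed scale they are smaller still: (0.13 / 3.92)² / (0.15 × 0.85) = 0.009 and (0.21 / 3.92)² / (0.30 × 0.70) = 0.014. The stated 0.2 and the stated intervals do not agree, so both sizes are carried forward.

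**3. What the estimator targets.** With arm as the only covariate, the exchangeable GEE solves, within each arm,

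p = Σ wᵢYᵢ / Σ wᵢmᵢ, with wᵢ = 1 / (1 + (mᵢ − 1)ρ),

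where Yᵢ is tests and mᵢ eligible relatives in family i. With ρ = 0 this is ΣYᵢ / Σmᵢ, the defined ratio. For illustration, a family of 4 in which two relatives test positive and each adds 3 grows to 10. At ρ = 0.2 its relatives weigh 1 / (1 + 9 × 0.2) = 0.357, against 1 / (1 + 3 × 0.2) = 0.625 in a family that stayed at 4.

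**4. Size at ICC 0.2** (simulated three-cycle cascade, control v intervention):

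| New relatives per positive | Tests / eligible | Exchangeable GEE | Shortfall by arm | Shortfall in difference |
|---|---|---|---|---|
| 1 | 16.4% v 32.5% | 14.8% v 29.7% | 1.6 and 2.8 | 16.1 − 14.9 = 1.2 |
| 2 | 18.3% v 35.2% | 14.3% v 28.9% | 4.0 and 6.2 | 2.2 |
| 3 | 20.3% v 37.7% | 13.8% v 28.1% | 6.5 and 9.6 | 17.4 − 14.3 = 3.1 |

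Odds ratios are 2.38–2.45 for the ratio and about 2.44 for the exchangeable fit. The exchangeable estimate is not the mean of family proportions either: with 3 new relatives that mean is 12.9% v 26.6%. In a software check, independence GEE equalled total tests over total eligible exactly.

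**5. Size at ICC 0.02, 3 new relatives:** 15.4% v 30.7% against 14.8% v 29.7%. The shortfall is 0.6 and 1.0 points by arm and 0.4 in the difference; the odds ratio is 2.43 both ways.

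**6. Controls.** At ICC 0 the two estimators agree. On cycle-1 relatives alone they agree at ICC 0, 0.02 and 0.2. With equal uptake in both arms (20%) at ICC 0.2, the exchangeable fit gives 18.5% v 18.4%, so it shows no spurious arm effect.

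**The case against.** **The headline size needs an ICC that the SAP's own intervals contradict.** This stands as a limit on magnitude. At an observed-scale ICC of 0.009, the gap is at most about 0.5 point per arm. But 0.2 is the value the SAP states, and the plan cannot rely on the smaller one until the two are reconciled.

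**Growth per positive is assumed.** This also stands. Many first-degree relatives of a positive parent or sibling are already counted through the index case. At 0.5 new relatives per positive, even ICC 0.2 gives only about 1 point per arm. Full follow-up is an upper bound as well: protocol 3.2 assesses at 6 months, while the Study duration text in 4.3 allows 12 months for three cycles.

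**The SAP asks for a marginal probability without specifying relative-level weighting.** Partly fair: the pooled ratio rises above the planning values because high-uptake families add relatives. But section 2 defines the outcome as tests over eligible relatives, and the exchangeable weighting, set by the estimated ρ, delivers neither that nor the family-level mean.

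**Two stronger readings are tempting.** A reader might infer that the odds ratio or the superiority test is compromised. The calculations do not support that: the odds ratio barely moves and the null comparison holds. A reader might also infer that cycle-1 relatives should become the primary population. That would drop relatives whom SAP section 3 includes in a trial of multigenerational screening. It would also remove the defect rather than estimate the defined outcome. Any remaining cycle-1 bias requires uptake to vary with family size, on which the documents are silent.

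**Conclusion.** The mismatch is real and follows from the documents' own definitions: the denominator grows with uptake, and the planned weighting discounts the growth. It affects the per-arm probabilities, their confidence intervals and the risk difference. The direction is downward whenever family uptake is positively correlated and positives add new eligible relatives.

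The size is uncertain. It ranges from about 1 point or less at the ICC implied by the prediction intervals to the several points tabulated at the stated 0.2, conditional on the assumed growth, beta distribution and full follow-up. The SAP's robustness statement is not wrong as worded; it does not address informative cluster size. The trial's ability to test for higher uptake is not in question. This should be corrected because the remedy is cheap and absolute uptake is a named primary output.

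**What to change.** In SAP section 4:

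- On all eligible ITT relatives, estimate per-arm uptake and detection, the risk difference and their confidence intervals by GEE with an independence working correlation and a robust variance clustered on family. This reproduces total tests over total eligible.
- Keep the exchangeable GEE for the odds ratio and its test, and say so. Using independence for the test on all cycles would cost about 2 to 11 points of power at ICC 0.2; one simulation gave 77% falling to 68%.
- Add a cycle-1-only analysis as a sensitivity analysis, since its denominator is fixed before any uptake. Do not substitute it for the primary population.
- State that relatives, not families, carry equal weight in the reported uptake, and that robustness to covariance misspecification does not extend to outcome-dependent family size.
- Reconcile the ICC of 0.2 with the prediction intervals in the Sample size entry.

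The cost is one option in the same software call and a few lines of text. No new data are needed, and the power of the main test is unchanged.

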#### 5. Secondary analyses

Subgroup analyses for participation will be performed by stratifying relatives according to the nature of familial relationship with their referent (i.e. parent, sibling or child of the referent), or by the type of referent, to assess the number of cascade cycles that generated the contact (i.e. cycle 1: direct referent is an index case; cycle 2: referent of referent is an index case etc).

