## Summary of changes between final and original statistical analysis plan from protocol

### V1.3, dated 10.08.2022

#### Sample size:

The sample size calculation originally described in the protocol V1.3, dated 10.08.2022 was slightly revised as follows . The revised calculation assumed an intraclass correlation coefficient of 0.2 to account for family effects. This translates into 95% prediction intervals for family-specific participation probabilities of 9 - 22% in the control arm, and 20 - 41% in the intervention arm. With these adjustment, the required sample size increased to 44 families per arm (vs 41 in the protocol V1.3, dated 10.08.2022).

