## **5 STATISTICS AND METHODOLOGY**

### **5.1. Statistical analysis plan and sample size calculation**

The sample size has been calculated according to the primary outcome, for each of the study groups, monogenic *positive* and *negative* FH. The statistician team of Unisanté ([name] and [name]) has estimated the sample size.

The aim of the study is to show that the proportion of people who agree to do the screening is higher in the experimental group than in the control group. Consents and refusals being measured within the families, the observations are not independent. Thus, it would be inappropriate to compare the consent rates of the control and experimental groups using a chi-square test. To account for the effect of clusters, proportions will be compared using an odds ratio that will be estimated using a logistic regression model. The latter will include the group as a fixed effect (the parameter of interest) and the family as a random effect.

For the monogenic *positive* FH group, we calculated that it will be necessary to include 41 families per group to show a statistically significant difference between the two groups with a significance level of 5% and a power of 90%, assuming that the consent rates for the control and interventional groups will be in mean equal to 0.15 respectively 0.3 and will be at 95% in the intervals [0.1,0.2] (range 0.05) respectively [0.1,0.5] (range 0.2) and that the number of contactable relatives will be in mean equal to 4.

For the monogenic *negative* FH group, we calculated that it will be necessary to include 36 families per group to show a statistically significant difference between the two groups with a significance level of 5% and a power of 90%, assuming that the consent rates for the control and interventional groups will be in mean equal to 0.5 respectively 0.7 and will be at 95% in the intervals [0.30,0.70] (range 0.4) respectively [0.46,0.86] (range 0.4) and that the number of contactable relatives will be in mean equal to 4.

These sample sizes were calculated analytically based on the standard errors of the mean proportions and were verified using simulations.

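### The subgroup analyses stratify by relationship and cascade cycle, but no test is planned of whether the arm effect differs between strata

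*Combined protocol and SAP*

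**What the plan says.** SAP section 5 is the whole subgroup plan: "Subgroup analyses for participation will be performed by stratifying relatives according to the nature of familial relationship with their referent" (parent, sibling or child), or according to the cascade cycle that generated the contact. It names no model, test, threshold or rule of interpretation.

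The only outcome model is in SAP section 4. It is a GEE with exchangeable correlation within families, giving participation probabilities per arm with 95% confidence intervals, "as well as the marginal odds ratio comparing the two arms". It contains no term for relationship or cycle.

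The SAP's summary of changes (Reporting) records that the subgroup analyses were new in the final SAP. Protocol V1.3 therefore has no earlier subgroup method to fall back on.

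Protocol section 4.3, on the differences between the monogenic positive and negative groups, opens a second cycle only after a relative's genetic test is positive, and allows at most three cycles. SAP section 3 counts relatives from later cycles in the population of interest.

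**The concern.** The usual reason to split by relationship is to learn whether the platform's effect depends on who is being contacted. That is a question about the difference between stratum effects. Separate estimates within strata do not answer it, for two reasons.

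- Each stratum holds only a fraction of the relatives. A stratum can miss significance through low power alone, with the same effect as its neighbours.
- One family can contribute a parent, a sibling and a child. The stratum estimates may therefore be correlated, and setting their separate confidence intervals side by side ignores that.

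The cycle split has a further difficulty. A relative enters cycle 2 only because someone in cycle 1 was tested and was positive. Uptake is the outcome that the intervention is meant to change, so the arms within later cycles are no longer protected by randomisation.

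At stake is a possible report that the platform works for some relationships and not for others when the data cannot support it. The overall comparison of arms is not at stake.

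**Working it through.** **Inputs from the documents**
- "significance level of 5% and a power of 90"% (protocol 5.1). The test is taken as two-sided; the documents do not say.
- "the consent rates for the control and interventional groups will be in mean equal to 0.15 respectively 0.3" (protocol 5.1).
- "the number of contactable relatives will be in mean equal to 4" (protocol 5.1).
- Families are "randomly assigned to a multigenerational patient-mediated genetic cascade screening (1:1) either" to the platform or to the local procedure (SAP section 1).
- "the required sample size increased to 44 families per arm" (SAP summary of changes), so 44 × 4 = 176 relatives per arm.

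**Assumptions.** Relationship shares are not given. Equal thirds are used first, then varied. The intraclass correlation is stated as 0.2, but the prediction intervals given beside it (9-22% and 20-41%) imply about 0.02 on the logit scale, so both are used.

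**Step 1: the plan's own figure.** Two proportions, pooled variance under the null, mean rate 0.225:

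n = [1.96·√(2·0.225·0.775) + 1.2816·√(0.15·0.85 + 0.30·0.70)]² / 0.15² = 160.8, so 161 relatives per arm.

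Families per arm = 161 × (1 + 3·ICC) / 4:
- ICC 0.02: 161 × 1.06 / 4 = 42.7, so 43, close to the stated 44.
- ICC 0.2: 161 × 1.6 / 4 = 64.4, so 65.

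The 44 thus agrees with the prediction intervals and not with the stated ICC. That is a separate matter, and it changes the subgroup result little.

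**Step 2: power within one stratum.** With equal thirds, n = 176/3 = 58.7 relatives per arm.

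Power = Φ{[0.15 − 1.96·√(2·0.225·0.775/58.7)] / √[(0.1275 + 0.21)/58.7]} = 0.49.

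At ICC 0.2, a family supplies 4/3 relatives per stratum on average. The design effect is 1 + (1/3)·0.2 = 1.067, the effective n is 55, and power is 0.47. Simulations with family-clustered tests at ICC 0.2 give slightly less, down to about 0.40.

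**Step 3: mixed significance under a uniform effect.** Treating the three strata as independent, with p = 0.494:
- all three significant: p³ = 0.12
- none significant: (1 − p)³ = 0.13
- mixed: 1 − 0.12 − 0.13 = 0.75

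Simulating 44 families per arm, which allows for correlation between strata, gives 0.75 with no family effect and 0.76 at a logit SD of 0.267 (latent ICC about 0.02). It gives 0.64 at a logit SD of 0.907 (latent ICC 0.2). A beta-binomial version gives 0.73 at ICC 0.02 and 0.63 at ICC 0.2. Replacing equal thirds by 20/40/40, or by two strata of 80/20 as a cycle split might give, the simulated range is 0.57-0.78.

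**Step 4: other uniform effects** (simulated over three splits and three levels of family spread)

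| Control v intervention | Mixed significance |
|---|---|
| 0.15 v 0.15 | 0.08-0.14 |
| 0.15 v 0.22 | 0.30-0.40 |
| 0.15 v 0.30 | 0.57-0.78 |
| 0.15 v 0.45 | 0.15-0.44 |
| 0.15 v 0.55 | 0.01-0.15 |

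The formula in step 3 places the region above one half roughly around the design value: 0.59 at an intervention uptake of 0.25, 0.62 at 0.35 and 0.34 at 0.40.

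**Step 5: with an interaction test.** A cluster-robust test of arm by subgroup at 5% declares a difference in 4-6% of the same simulated trials (0.038-0.065).

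**Step 6: what that test can detect.** The variance of one stratum's log odds ratio is about 1/(58.7·0.1275) + 1/(58.7·0.21) = 0.215. The difference between two strata has standard error √(2·0.215) = 0.66, ignoring clustering. A 95% interval is then about ±1.28 on the log scale. The whole planned effect is ln[(0.30/0.70)/(0.15/0.85)] = 0.89. The interaction test therefore has low power.

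**The case against.** The best reply is that the SAP plans estimation and sets no significance rule for strata. Section 5 is one sentence, section 4 asks for probabilities and an odds ratio with intervals, and no claim of a differential effect is announced. The cycle split can be read as descriptive already. The replacement test has low power, so its main benefit is discipline in reporting.

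Much of this stands. A reader might infer that a uniform effect will usually look like a subgroup difference, whatever the truth. The documents do not support that. It holds only if the true effect is near 0.15 against 0.30 and strata are judged by significance. Step 4 shows mixed results in fewer than half of trials with no effect, with a smaller effect (0.15 v 0.22) and with a clearly larger one (0.15 v 0.45 or more). A reader might also infer that the SAP intends to compare strata by p-value, and it does not say so.

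The reply does not supply a method for the subgroup question. Estimates within strata, with or without p-values, leave the difference between strata unestimated. Nothing in the SAP stops a reader from contrasting them. Low power argues for a cautious label and not for leaving the contrast out.

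**Conclusion.** The concern holds in a limited form. No comparison of effects between strata is planned, and the stratified analysis cannot replace one. At the design effect, with relationship shares assumed equal and ICC between about 0 and 0.2, each relationship stratum has about 40-49% power. About 63-75% of trials with a uniform effect would show mixed significance, against a false-positive rate of 4-6% for an interaction test. The larger figure is conditional on an effect near the planned one and on comparison by significance, so it should not be quoted as a general rate.

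The point about cycles rests on the protocol's own cascade rule and needs no assumption about shares: membership beyond cycle 1 follows from earlier uptake and a positive test. The primary and secondary outcome analyses over all relatives are not affected by the missing interaction test.

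**What to change.** Amend SAP section 5 as follows.

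- Fit one GEE clustered on family with arm, relationship and arm-by-relationship terms. Report the interaction estimate and test, with stratum odds ratios and 95% confidence intervals from that same model.
- Use cycle-1 intention-to-treat relatives, at least for the main version, so that stratum membership does not depend on earlier uptake. A version over all cycles can follow as a supplement.
- Report uptake by cycle descriptively, without a comparison of arms presented as a treatment effect.
- Label the analysis exploratory and state that no subgroup difference will be claimed without the interaction result.

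The cost is some wording and one extra model, with no new data. The interaction test has low power, so a non-significant result will not show that the effect is the same in all relationships. The SAP should say so. Restricting the main version to cycle 1 also leaves out later-cycle relatives who belong to the population in SAP section 3, and this should be stated.
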